**What impact does the New Zealand maternity care model have on fetal and neonatal outcomes? A retrospective cohort study comparing exclusive midwife led care with a shared care model.**

Background

New Zealand has a maternity system that has undergone a number of changes in the past twenty years that have moved it away from a medical model of care and towards a midwifery model [18]. The changes have been the subject of scrutiny and controversy focusing on questions related to the safety of the system [3, 5, 6, 7, 15, 16, 17, 20, 22]. Despite this, there has been little in the way of systematic evaluation that specifically relates to the safety of the maternity system [8, 10-14, 19].

New Zealand’s maternity system is based on a midwife-led care model, whereby midwives practice with a level of autonomy higher than most of their overseas counterparts [9, 21, 23]. International literature has generally supported the safety of the midwife-led care model [4]. However this does not provide sufficient evidence to support the safety of the New Zealand system, as in many countries where the international literature was based midwives have less autonomy than they do in New Zealand; so even in midwife-led births there is some medical input. The uniqueness of our system means that evaluation of the safety of New Zealand based midwife-led care needs to be addressed within New Zealand.

Along with the lack of New Zealand based research, impetus for research in this area has been provided by a recently published Dutch study [1]. Holland has a maternity system that is similar to ours in that midwives practice with a high level of autonomy; therefore evaluation in a Dutch context is relevant to us. The Dutch study found, most significantly, that “*infants of pregnant women at low risk whose labour started in primary care under the supervision of a midwife had a significant higher risk of delivery related perinatal death than infants of pregnant women at high risk whose labour started in secondary care under the supervision of an obstetrician… relative risk 2.33*” [1, p. 1]. Given the similarities between the Dutch maternity system and ours, this is a concerning finding in the New Zealand as well as Dutch context.

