iii) To calculate and compare (where relevant) the incidence of potentially avoidable serious early neonatal morbidity and perinatal mortality, overall, and 1) in women whose LMC is reported as being a midwife where there is no evidence of medical input, 2) in women whose LMC is reported as being a midwife where there is evidence of medical input and 3) in women whose LMC is a general practitioner or obstetrician.

Inclusion criteria

- Singleton pregnancy
- Delivered during a specified time period (likely to be 1^st^ January 2006 and 1^st^ January 2010, The final inclusion period will be based on DHB birthing numbers and required sample size)
- Birthed at one of six specified District Health Boards
- Equal to or greater than 37 weeks gestation
- No identified major fetal or neonatal congenital, chromosomal, or metabolic abnormalities.

The sample size has been determined based on power calculations using the rarest outcome in the study, intrapartum fetal death. Sample size has been calculated using the Fleiss method with continuity correction in OpenEpi. Outcome rates have been estimated based on the Dutch Perinatal Mortality Study. An adequately powered simple study requires a sample size of 48 878. However, we need to increase the sample size because we wish to adjust the results for several major confounders particularly maternal age, antenatal risk, ethnicity, deprivation and parity of the mother. Furthermore, we wish to perform some subgroup analysis. For these reasons, we plan to double the sample size.

Exposure

- Reference group

Women who are reported to have a midwife as Lead Maternity Carer at booking and at admission in labour and where there is no evidence of medical input.

- Comparison groups

Women who are reported to have a midwife as LMC with evidence of medical input. Women will be included in this group if they have had one or more secondary care consultations or if they have had any antenatal admissions to hospital.

- Women who have had a General Practitioner, private obstetrician, or secondary care team as their LMC.

Outcomes

- Antepartum stillbirth: Antepartum stillbirth rates will be calculated as the number of fetal deaths that occur before the onset of labour divided by the total number of births in our cohort.

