- Intrapartum mortality: Intrapartum mortality rates will be calculated as the number of fetal deaths that occur after the onset of labour but before delivery divided by the total number of births in our cohort, not including antenatal still births.
- Early neonatal mortality: Early neonatal mortality rates will be calculated as the number of early neonatal deaths, that is deaths that occur post-delivery and within seven days of life, divided by total number of births in our cohort, not including antenatal still births or babies who have died in the intrapartum period.
- Neonatal admission to a specialist neonatal unit: Neonatal admission rates will be calculated as the number of babies admitted to a specialist neonatal unit within the first seven days of life divided by the total number of births in our cohort but not including antenatal stillbirths, or babies dying intrapartum, or in the early neonatal period.
- Low Apgar score: Rates of low Apgar score will be calculated as the number of babies born with an Apgar score at five minutes post-delivery of below seven, divided by total number of births in our cohort, not including antenatal still births or babies who have died in the intrapartum period.
- Birth related asphyxia: Rates of birth related asphyxia will be calculated based on the number of babies identified with the condition by ICD-10-AM codes P210, P211, P219, divided by total number of births in our cohort, not including antenatal still births or babies who have died in the intrapartum period.
- Intrauterine hypoxia: Rates of intrauterine hypoxia will be calculated based on the number of babies identified with the condition by ICD-10-AM codes P200, P201, P209 divided by total number of births in our cohort, not including antenatal still births or babies who have died in the intrapartum period.
- Hypoxic ischaemic encephalopathy: Rates of hypoxic ischaemic encephalopathy will be calculated based on the number of babies identified with the condition by ICD-10-AM code P916, divided by total number of births in our cohort, not including antenatal still births or babies who have died in the intrapartum period.

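### Intrauterine hypoxia and HIE are measured only in babies who survive labour, so their odds ratios need a pre-specified composite with intrapartum death beside them

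*SAP*

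**What the plan says.** The third objective is to compare the "incidence of potentially avoidable serious early neonatal morbidity and perinatal mortality" between care groups. The Outcomes section then defines each outcome with its own denominator:

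- **Intrapartum mortality:** "number of fetal deaths that occur after the onset of labour but before delivery divided by the total number of births in our cohort", leaving out antenatal stillbirths only.
- **Intrauterine hypoxia:** babies identified by any of "P200, P201, P209 divided by total number of births in our cohort, not including antenatal still births or babies who have died in" labour.
- **HIE:** babies identified by "code P916, divided by total number of births in our cohort, not including antenatal still births or babies who have died in the intrapartum" phase.

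Birth asphyxia and low Apgar score have the same denominator as the last two. The numerators are not expressly limited to babies alive at delivery, but a rate over that denominator implies it.

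The Analysis section plans logistic models giving an odds ratio for each major outcome, shared v midwife-only care. No outcome combines intrapartum death with hypoxic morbidity. Nothing says how the morbidity odds ratios are to be read if intrapartum mortality differs between groups. The sample-size paragraph rests on "power calculations using the rarest outcome in the study, intrapartum fetal death".

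**The concern.** Surviving labour happens after exposure and is itself, in mirror image, a study outcome. Restricting the hypoxia outcomes to survivors of labour therefore compares groups selected by something the care model may change. A fetus that becomes hypoxic and dies in labour counts as a death and leaves the hypoxia rate. One that becomes equally hypoxic and is delivered alive stays in it. If one model turns some deaths into live births with injury, its morbidity rate rises although total hypoxic harm is unchanged or lower.

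The condition for this is a difference in intrapartum mortality, and that is the outcome on which the study is sized. At stake is the interpretation of two of the outcomes closest to the study's question about safety in labour: a reader could meet a mortality odds ratio favouring one model and an HIE odds ratio favouring the other, with no pre-specified measure of the total.

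**Working it through.** **The plan's own figure.** The SAP states a required sample of 48 878 and says "Sample size has been calculated using the Fleiss method with continuity correction in OpenEpi". It gives no event rates, alpha, power or group ratio, so the figure cannot be reproduced. Nothing below depends on it except the illustrative group size used in weighing the counter-argument. The SAP's only effect size is "relative risk 2.33" (Background), which is for delivery-related perinatal death in the Dutch study, not intrapartum death alone. All rates below are assumptions.

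**Check 1: HIE with equal total harm.** Let s be the proportion of births with severe intrapartum hypoxic injury, equal in both groups, and d the fraction of these who die in labour. Those who survive labour are counted as HIE.

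- Survivor-only rate = s(1−d)/(1−sd)
- Odds = s(1−d)/(1−s), so the odds ratio, shared v midwife-only, is (1−d_shared)/(1−d_midwife). It does not depend on s.

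With s = 1.5 per 1000:

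| d, midwife-only v shared | Intrapartum deaths per 1000 | HIE per 1000 survivors | Survivor-only OR | OR, death or HIE |
|---|---|---|---|---|
| 25% v 15% | 0.375 v 0.225 | 1.13 v 1.28 | 0.85/0.75 = 1.13 | 1.00 |
| 30% v 10% | 0.45 v 0.15 | 1.05 v 1.35 | 0.90/0.70 = 1.29 | 1.00 |
| 40% v 20% | 0.60 v 0.30 | 0.90 v 1.20 | 0.80/0.60 = 1.33 | 1.00 |

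The last column is 1.00 because the composite rate over births alive at the onset of labour is s in both groups. If d is equal in the two groups, the survivor-only odds ratio is also 1.00.

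**Check 2: dependence on how common the morbidity is.** Let intrapartum deaths be d0 and d1 per 1000, with d1 = 2.33 × d0 (ratio borrowed as an assumption). Let h per 1000 be the non-fatal hypoxia cases in the group with more deaths. Total harm is set equal, h + d1 in both groups, treating every intrapartum death as hypoxic. The survivor-only ratio, higher- v lower-mortality group, is [h/(1000−d1)] / [(h+d1−d0)/(1000−d0)]. For h = 2, d0 = 0.5 and d1 = 1.165 this is (2/998.835)/(2.665/999.5) = 0.75.

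| d0 v d1 per 1000 | h = 2 | h = 10 |
|---|---|---|
| 0.2 v 0.466 | 0.88 | 0.97 |
| 0.5 v 1.165 | 0.75 | 0.94 |
| 1 v 2.33 | 0.60 | 0.88 |

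The distortion is sizeable when the morbidity is about as rare as intrapartum death, and small near 10 per 1000.

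**Check 3: the denominator by itself.** Removing intrapartum deaths from the denominator alone changes the ratio by (1−d0/1000)/(1−d1/1000), which is 1.0003 to 1.0013 over the same inputs, or 0.03% to 0.13%. Any material effect comes from cases lost from the numerator.

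**The case against.** The strongest reply has three parts.

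**HIE has its natural population at risk.** It is diagnosed in a newborn, and the objective names early neonatal morbidity separately from perinatal mortality. This stands. A reader might infer that the HIE denominator is an error, but the documents do not support that. For intrauterine hypoxia the reply is weaker: the condition arises in the fetus, the study aim covers fetal as well as neonatal outcomes, and the SAP gives no reason for leaving out those who die in labour.

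**The deaths are not lost.** Intrapartum mortality is an outcome in its own right, so a reader who concludes that a model with more deaths would simply look safer goes too far. Take the doubled sample as two equal groups of 48 878 (the split is an assumption) and apply Check 1, with midwife-only care first in each count:

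- 30% v 10%: deaths about 22 v 7 (p about 0.01); HIE 51 v 66, OR 1.29 (95% CI 0.89 to 1.85).
- 40% v 20%: deaths about 29 v 15 (p about 0.03); HIE 44 v 59, OR 1.33 (0.90 to 1.97).
- 25% v 15%: deaths about 18 v 11 (p about 0.18); HIE 55 v 62, OR 1.13 (0.79 to 1.63).

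In the first two cases mortality shows the harm and the HIE result is inconclusive. In the third neither is conclusive and they point in opposite directions, so reading them side by side does not settle the matter. The composite is 48 878 × 0.0015 = 73 v 73, OR 1.00. Separate reporting softens the problem without removing it.

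**Counting every intrapartum death as intrauterine hypoxia would assign a cause without evidence.** This stands too. Such deaths need not all be hypoxic, and nothing in the SAP would justify the relabelling. A composite labelled as death or hypoxia avoids it.

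**Conclusion.** The point holds as a competing-event problem. The intrauterine hypoxia and HIE odds ratios depend on surviving labour, and the plan has no combined measure and no rule for reading them beside intrapartum mortality. It is conceptually strongest for intrauterine hypoxia.

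The size cannot be fixed from the SAP. Under the Check 1 assumptions (equal total injury, and the stated differences in the fraction dying in labour) the spurious HIE odds ratio is about 1.13 to 1.33. Under Check 2, a morbidity near 10 per 1000 gives ratios of 0.88 to 0.97.

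A reader might infer that these odds ratios will point the wrong way. The documents do not show that: it requires a difference in intrapartum mortality and near-equal or opposing total harm, and neither is known. Nor do they show that a composite must replace the planned outcomes as the main hypoxic outcome. What is supported is a low-cost addition to the plan.

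**What to change.** 1. Keep the coded HIE and intrauterine hypoxia rates as defined.
2. Pre-specify two composites, intrapartum death or HIE and intrapartum death or intrauterine hypoxia, over all births alive at the onset of labour. This is the SAP's existing intrapartum-mortality denominator. Show the components beside each composite.
3. Do not relabel intrapartum deaths as intrauterine hypoxia.
4. State in the Analysis section that the survivor-only odds ratios are conditional on surviving labour and are to be read beside intrapartum mortality.

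The cost is SAP text and two further models, since every component is already an outcome. There are two downsides. The composites mix death with morbidity, hence the need to show components. They also need antepartum and intrapartum stillbirth to be told apart, for which the Outcomes part of Available data says the mortality review committee's data may be required. The existing intrapartum mortality outcome already carries that dependence.

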- Low birth weight: Where the birth weight was recorded as less than 2500 grams. This variable was included as a negative control outcome in order to determine whether adjustment for confounding for the main outcomes was likely to have been sufficient. This is on the assumption that model of care is unlikely to substantially affect birth weight directly, but similar confounders may affect the relation between low birth weight, model of care and the outcomes

Covariates

The study will collect a number of maternal variables that may be potential confounders or mediators. These include:

- Maternal age: 12-18 yrs; 19-25 yrs; 26-35 yrs; 36-40 yrs and 40+.
- Ethnicity: NZ European, Māori, Pacific Island, Asian, Other.
- Deprivation: NZ Dep quartiles.
- Parity before delivery: 0, 1, 2, 3, 4+.
- Gestation at delivery: 37/40-38/40; 39/40-40/40; 41/40; 42+ weeks.
- Location of delivery: Primary birthing unit, secondary or tertiary hospital.
- Mode of delivery: Normal vaginal delivery, instrumental delivery, caesarean section.
- Pre-existing diabetes and/or hypertension: yes, no.

Analysis

- We will first calculate incidence rates (and 95% confidence intervals) of all outcomes for all groups combined and then for each group separately.
- We will then develop logistic regression models to calculate odds ratios (and 95% confidence intervals) for each major outcome comparing women receiving shared compared with midwife only care. The models will include potentially confounding patient characteristics such as age, parity, ethnicity and presence of pre-existing conditions.

Available data

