1. EXPOSURE

For classifying the exposure status LMC data will be collected from individual DHBs. This category is the only one not available from the MOH who only hold LMC data for around 70% of women.

It is difficult to know how robust/complete the DHB data is before accessing it. Generally it is entered by clinicians. The available categories are as follows:

- LMC data:

LMC at booking

LMC at admission in labour

Labour care provided by*

Delivered by

Labour and delivery assisted by

*The last three are not collected by all the DHBs.

- Data to classify ‘medical input’:

A woman will be classified as having medical input if she has had antenatal secondary care consultations. This data is held by the MOH and comes from the National Non- Admitted Patient Collection. We will analyse the number of secondary care consultations and the type of consultation. The following codes are relevant:

| W03002 | First obstetric consults |
| --- | --- |
| W03003 | Subsequent obstetric consults |
| W03005 | Amniocentesis |
| W03006 | Chorion villis sampling |
| W03007 | Rhesus Clinics - multidisciplinary clinics |
| W03008 | Maternity foetal medicine clinics - multidisciplinary clinics |
| W03009 | Foetal medicine / anomalies clinics - multidisciplinary clinics |

Some of these categories are more likely to be associated with greater obstetric input; number of consults is also relevant. For example a woman who has one consult recorded under amniocentesis and no further consults likely had a negative test and limited obstetric input in her care. Sub-category analysis will therefore be necessary.

The number of obstetric related hospital admissions within the pregnancy is also available from the NMDs. These data are not detailed and we will be making the assumption that if a patient has been admitted to hospital she will have had some level of secondary care input. Again number of admissions is relevant and sub-category analysis necessary.

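### The rate intervals and logistic models make no allowance for births that share a carer, so if outcomes correlate within carers the intervals for the commoner morbidity outcomes will be too narrow, mainly for group rates and for comparisons with the GP/obstetrician/secondary-team group

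*SAP*

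**What the plan says.** The Analysis section has two steps. The first is descriptive: "We will first calculate incidence rates (and 95% confidence intervals) of all outcomes for all groups combined and then for each group separately". The second is "We will then develop logistic regression models to calculate odds ratios (and 95% confidence intervals) for each major outcome", with the contrast given as "comparing women receiving shared compared with midwife only care". On adjustment it says: "The models will include potentially confounding patient characteristics such as age, parity, ethnicity and presence of pre-existing conditions". No carer, mother or DHB term is named, and no random effect, GEE or robust variance. The method for the rate intervals is not stated.

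Under Outcomes, the unit is the birth: the antepartum stillbirth rate, for example, is "divided by the total number of births in our cohort". The Inclusion criteria take singleton births in six DHBs over a provisional window ("likely to be 1^st^ January 2006 and 1^st^ January 2010") and do not limit a woman to one birth.

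On sample size: "Sample size has been calculated using the Fleiss method with continuity correction in OpenEpi". The result, 48 878, is then doubled for confounder adjustment and subgroups; clustering is not among the reasons.

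Under Exposure, the reference group is midwife LMC with no medical input. The first comparison group is midwife LMC with at least one secondary consultation or any antenatal admission. The second is defined by who the LMC is: a GP, a private obstetrician or a secondary care team. In Available data, "For classifying the exposure status LMC data will be collected from individual DHBs"; the items listed include LMC at booking and at admission in labour. Whether individual carers can be identified is not said.

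**The concern.** One LMC may look after many women in a four-year cohort. Carer practice may plausibly influence outcomes that depend on judgement or recording, such as neonatal unit admission, Apgar scoring, and coded asphyxia or hypoxia. Births under the same carer are then correlated, and a variance formula that treats them as independent overstates precision. The same mother can also enter twice.

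The Background says the results may be used either to defend midwife-led care or to prompt further research into its risks. Intervals that are too narrow could let variation between individual carers pass for a difference between models of care. The question is which of the planned estimates are exposed to this, and by how much.

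**Working it through.** **The plan's own figure.** The 48 878 cannot be reproduced, because alpha, power, group ratio and outcome rates are not given. Solving backwards with the only printed effect (relative risk 2.33, for delivery-related perinatal death), two-sided 5% and the continuity correction, 1:1 groups need a reference rate of about 0.66 per 1000 at 80% power or 0.87 per 1000 at 90%. Neither rate is printed. Doubling gives 2 × 48 878 = 97 756. The Fleiss formula is for two independent proportions.

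**Assumptions (none in the SAP).** Caseload m = 160 births per carer (about 40 a year for 4 years), outcome risk 4%, outcome ICC ρy = 0.01, half of each midwife's women with medical input, and within-carer correlation of that exposure ρx = 0.05 to 0.2. ICC 0.01 means a between-carer SD of √(0.01 × 0.04 × 0.96) = 0.0196, about 2 percentage points on a mean of 4%.

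**1. Group rates.** A midwife group holds about half of each caseload. Design effect = 1 + (m − 1)(0.5 + 0.5ρx)ρy. With ρx = 0.1: 1 + 159 × 0.55 × 0.01 = 1.87, square root 1.37. Coverage of the plain 95% interval = 2Φ(1.96/1.37) − 1 ≈ 0.85. Simulation (80,000 births, 1,500 datasets) gave 0.84-0.86 across the range of ρx. For all groups combined, whole caseloads count: 1 + 159 × 0.01 = 2.59, and coverage is about 0.78.

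**2. Contrast fixed by carer type.** Design effect 2.59, so the true SE is √2.59 = 1.61 times the plain SE. This takes whole caseloads of equal size on both sides. If the midwife arm holds only half-caseloads (1 + 79 × 0.01 = 1.79, square root 1.34), the ratio lies between 1.34 and 1.61. A separate simulation (500 carers × 196 births, carer SD 0.3-0.5 on the logit scale, 3,000 runs) gave:

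| Outcome risk | True SE / plain SE | Coverage of plain 95% interval |
|---|---|---|
| 5% | 1.36-1.91 | 84-70% |
| 1% | 1.11-1.27 | 93-87% |
| 0.5 per 1000 | 0.99-1.03 | 96-95% |

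**3. Midwife with versus without medical input.** Both arms sit within one caseload. Variance factor = 1 + (m − 1)ρxρy; false-positive rate = 2[1 − Φ(1.96/√factor)].

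| ρx | Factor | Formula | Simulated |
|---|---|---|---|
| 0.05 | 1.08 | 5.9% | 5.5% |
| 0.1 | 1.16 | 6.9% | 6.5% |
| 0.2 | 1.32 | 8.8% | 8.2% |

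At ρx = 0 the factor is 1 and the test is nominal. In the second simulation the SE ratio was 0.99-1.01 with equal referral share across midwives. With varying share (logit SD 0.7) it was 1.01-1.04 at 1% risk and 1.07-1.13 at 5%.

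**4. Deaths.** At 0.5 per 1000 a carer SD of 0.5 on the logit scale gives an ICC of about 0.25 × 0.0005 = 0.000125. The design effect at m = 160 is then 1 + 159 × 0.000125 = 1.02, so the SE is about 1% larger.

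**5. Repeat mothers.** If a share s of births comes from women with two births, design effect = 1 + s × ICC. For s = 0.1-0.3 and ICC 0.02-0.3 this is 1.002-1.09. Interval width grows by at most √1.09 = 1.044, about 4%.

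**The case against.** The strongest objection is that the main contrast is largely protected. Medical input is assigned woman by woman, so a midwife's own effect falls on both arms and mostly cancels. This stands: a reader might infer that exposure belongs to the carer throughout, but the SAP supports that only for the GP/obstetrician/secondary-team group.

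A reader might also infer a badly inflated error rate. With ICC 0.05 the simulated false-positive rate for the midwife contrast reaches 15% at ρx = 0.1 and 23% at ρx = 0.2. But at 4% risk that ICC implies a between-carer SD of √(0.05 × 0.04 × 0.96) = 4.4 points, larger than the mean itself. Nothing in the SAP points to so wide a spread. A carer SD of 0.3-0.5 on the logit scale corresponds to an ICC of about 0.004-0.01 at this risk.

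A third inference is that the sample size is undermined. It was set by intrapartum fetal death, where the effect is negligible.

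Three further points stand. Independence of births is the default reading of plain logistic regression, not something the SAP declares for its models. The simulations are unadjusted, and patient covariates could remove part of the within-carer correlation. The SAP does not show that a carer code exists, and a secondary care team may have no single carer to cluster on.

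None of this protects the rate intervals or a contrast fixed by carer type.

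**Conclusion.** The concern holds in a limited form. If outcomes correlate within carers, following the plan as written gives intervals that are too narrow for neonatal unit admission, and for low Apgar and coded asphyxia or hypoxia to the extent that these are common. The estimates exposed are the incidence rates, where plain 95% intervals for a midwife group cover about 85%, and any contrast fixed by carer type, with a true SE up to about 1.6 times the plain SE. The Analysis wording leaves open whether shared care includes the GP/obstetrician/secondary-team group, but objective iii lists that group for comparison.

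For midwife care with versus without medical input the inflation is modest, and close to nil if midwives refer at similar rates. It is negligible for mortality, and repeat births add little. All sizes rest on an assumed caseload, ICC, risk and referral pattern. A claim that every interval in the study is too narrow is not supported.

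**What to change.** In the Analysis section, state that the unit is the birth and that the odds ratios and group rates for the morbidity outcomes will have cluster-robust (sandwich or GEE) standard errors. Cluster on a pseudonymised carer code requested in the DHB extract already planned, with a team-level code for secondary care teams. In both simulations cluster-robust errors brought error rates and coverage close to nominal.

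Where a DHB cannot supply a code, cluster on the mother's identifier, enter DHB as a fixed effect (six DHBs are too few for sandwich errors at that level), and report unmodelled carer clustering as a limitation.

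The cost is some SAP wording, a model option, somewhat wider intervals for the commoner outcomes, and one extra requested field whose availability is not established. The robust errors themselves leave the planned point estimates unchanged; under the fallback, the DHB term would alter the adjusted odds ratios. The sample size need not change on this account.

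### Three exposure groups are set up, but the regression makes one contrast against an undefined 'shared' group, so the medical-LMC group gets no separate adjusted estimate

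*SAP*

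**What the plan says.** **Objective iii** plans to calculate and, where relevant, compare incidence in three groups. The third is described as "3) in women whose LMC is a general practitioner or obstetrician".

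**Exposure** describes the reference category as follows: "Women who are reported to have a midwife as Lead Maternity Carer at booking and at admission in labour and where there is no evidence" (that is, nothing on record to show that a doctor was involved). It adds two comparison groups. The first is "Women who are reported to have a midwife as LMC with evidence of medical input", meaning at least one secondary care consultation or any antenatal hospital admission. The second is "Women who have had a General Practitioner, private obstetrician, or secondary care team as their LMC".

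**Analysis** has two steps. Incidence rates with 95% confidence intervals are given "for all groups combined and then for each group separately". Logistic models then give odds ratios for each major outcome, "comparing women receiving shared compared with midwife only care", with terms for potential confounders such as age, parity, ethnicity and pre-existing conditions.

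**Title and Background.** The title compares exclusive midwife-led care with a shared care model. The Background is prompted by a Dutch midwife-versus-obstetrician result (relative risk 2.33) and considers what would follow if midwife-led care did worse than medical care.

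**The concern.** A group listed for comparison has no place in the only adjusted analysis, or has one only by being absorbed into a term that the SAP does not define. The sample-size paragraph says that results need adjustment for major confounders (maternal age, antenatal risk, ethnicity, deprivation, parity). By the plan's own reasoning, crude rates cannot settle how midwife-only care compares with care led by a doctor or hospital team.

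The boundary of the third group is also open, as is the boundary between the two comparison groups. An analyst could follow the text faithfully and reach different group counts and different odds ratios, with the choice made after the data are seen. The main exposure of the study is therefore not fixed in advance.

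**Working it through.** The point rests on the text. The arithmetic in steps 4 and 5 only shows what can and cannot be said about size.

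**1. What each group receives**

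| Group | Objective iii | Exposure | Rates with CI | Adjusted OR |
|---|---|---|---|---|
| Midwife LMC, no medical input | yes | reference | yes | reference |
| Midwife LMC, medical input | yes | comparison | yes | yes, if this is 'shared' |
| Medical LMC | GP or obstetrician | GP, private obstetrician or secondary care team | yes | none of its own |

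There are two readings of 'shared'. (a) It means the second group only: the third group then has no adjusted result. (b) It means both comparison groups: the third group then contributes to a pooled odds ratio but has none of its own. Neither reading yields an adjusted midwife-only v medical-LMC estimate.

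**2. Membership of the third group.** Objective iii says "in women whose LMC is a general practitioner or obstetrician". Exposure names private obstetrician and secondary care team as separate items. Women whose LMC is the secondary care team are in the group under Exposure and have no clear place under Objective iii.

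**3. Overlap.** Only the reference group is tied to time points. Take a woman with a midwife as LMC at booking, one secondary care consultation, and the secondary care team as LMC on admission in labour.
- Reference group: excluded, because the LMC on admission is not a midwife.
- Second group: fits, because a midwife was reported as LMC and there was a consultation.
- Third group: fits, because she has had the secondary care team as LMC.

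**4. Does pooling have a known direction?** Let s be the third group's share of a pooled 'shared' group, and RR2 and RR3 the relative risks of the second and third groups against midwife-only. Then pooled RR = (1 − s)·RR2 + s·RR3. Assume RR2 = 1. The values of RR3 and s are also assumptions.

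| s | RR3 = 1/2.33 = 0.429 | RR3 = 2.33 |
|---|---|---|
| 0.1 | 0.943 | 1.133 |
| 0.3 | 0.829 | 1.399 |
| 0.5 | 0.715 | 1.665 |

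For example, 0.7 × 1 + 0.3 × 0.429 = 0.829. The pooled figure can fall on either side of 1 and does not recover RR3.

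**5. Sample size, for context.** The SAP states: "An adequately powered simple study requires a sample size of 48 878". It then doubles this, 2 × 48,878 = 97,756. It names the Fleiss method with continuity correction but gives no alpha, power, rates or allocation. With k the allocation ratio, p̄ the weighted mean proportion and d = |p1 − p2|:

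n = [z_α·√((1 + 1/k)·p̄(1 − p̄)) + z_β·√(p1(1 − p1) + p2(1 − p2)/k)]² / d²

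n_cc = (n/4)·[1 + √(1 + 2(k + 1)/(n·k·d))]²

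Assume two-sided 5%, 80% power, 1:1, RR 2.33 and rates of 0.664 v 1.547 per 1000. Then n = 22,227, n_cc = 24,439 and the total is 48,878. The same total is reached, within rounding of the base rate, at 0.708 or 0.780 per 1000 (the two 1:2 splits), at 0.814 or 0.942 (the two 1:3 splits), and at 0.869 with 90% power and 1:1. The figure therefore does not identify the allocation.

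To show what a separate third-group contrast might offer, assume 97,756 births, rates of 0.664 v 1.547 per 1000, and the two midwife groups of equal size. Unadjusted power for midwife-only v the third group, depending on which has the higher rate, is:

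| Third-group share | Births | Power |
|---|---|---|
| 25% | 24,439 | 86–88% |
| 15% | 14,663 | 70–78% |
| 10% | 9,776 | 51–68% |
| 5% | 4,888 | 19–48% |

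**The case against.** The best defence is that the study never promised this contrast. Its title compares exclusive midwife-led with shared care, which is what the regression models. Objective iii compares only where relevant, and the third group does receive its own rates with confidence intervals. Keeping that group descriptive would be a legitimate choice. This stands as far as it goes, but the SAP does not make that choice: it lists the group under comparison groups and nowhere calls it descriptive only. One could also say that 'obstetrician' in Objective iii loosely covers hospital teams. The separate listing in Exposure makes that doubtful, and the sections still need to agree.

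Three stronger readings might be inferred and are not supported.
- *That 48,878 fits only two equal groups.* It does not: several allocations and base rates give the same total, and the SAP states none of them. The ratio of 2.33 is also quoted for delivery-related perinatal death, whereas the study is sized on intrapartum fetal death.
- *That pooling makes midwife care look safer.* The documents fix no direction, and the illustration goes both ways.
- *That the third-group contrast is shown to be underpowered.* The power figures rest on assumed rates and shares.

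The overlap is confined to women who change LMC, and the SAP does not say how many there are.

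**Conclusion.** The point holds on the text. As written, the plan gives one of its two comparison groups no separate adjusted estimate for any outcome, leaves 'shared' undefined, describes the third group in two ways, and allows some women into both comparison groups. These conclusions need no numerical assumption. What cannot be concluded is how large any distortion would be or which way it would run: the pooled relative risks of 0.72 to 1.67 and the power range of 19% to 88% are illustrations on assumed inputs. The third group is not dropped from the study; it is missing from the adjusted analysis as a group in its own right.

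**What to change.** 1. In Analysis, fit exposure as a multi-level factor in every model, with midwife-only as reference, and report an adjusted odds ratio with 95% confidence interval for each comparison group. If the sponsor prefers the third group to be descriptive, the SAP should say so, give the reason, and draw no adjusted midwife v medical conclusion.
2. Define 'shared' as midwife LMC with medical input.
3. Use one definition of the third group in Objective iii and Exposure, stating whether the secondary care team belongs to it.
4. Make the groups mutually exclusive with a rule that uses LMC both at booking and on admission in labour, and state where women who change LMC are placed. A rule based on booking alone would contradict the reference group, which requires a midwife at both points.
5. Where the DHB fields allow, report secondary-care-team women separately as a sensitivity analysis.

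**Cost.** SAP wording and one recoded variable. LMC at booking and on admission are both among the DHB categories listed under Available data. That section also warns that completeness is unknown before access, and it does not show that the fields separate private obstetricians from the secondary care team. The statistical price is a wide interval for rare outcomes if the third group is small.
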